## Abstract

**Background:**

The magnitude of safety risks related to medications of the older adults has been evidenced by numerous studies, but less is known of how to manage and prevent these risks in different health care settings. The aim of this study was to coordinate resources for prospective medication risk management of home care clients ≥ 65 years in primary care and to develop a study design for demonstrating effectiveness of the procedure.

**Methods:**

Health care units involved in the study are from primary care in Lohja, Southern Finland: home care (191 consented clients), the public healthcare center, and a private community pharmacy. System based risk management theory and action research method was applied to construct the collaborative procedure utilizing each profession’s existing resources in medication risk management of older home care clients. An inventory of clinical measures in usual clinical practice and systematic review of rigorous study designs was utilized in effectiveness study design.

**Discussion:**

The new coordinated medication management model (CoMM) has the following 5 stages: 1) practical nurses are trained to identify clinically significant drug-related problems (DRPs) during home visits and report those to the clinical pharmacist. Clinical pharmacist prepares the cases for 2) an interprofessional triage meeting (50–70 cases/meeting of 2 h) where decisions are made on further action, e.g., more detailed medication reviews, 3) community pharmacists conduct necessary medication reviews and each patients’ physician makes final decisions on medication changes needed. The final stages concern 4) implementation and 5) follow-up of medication changes. Randomized controlled trial (RCT) was developed to demonstrate the effectiveness of the procedure.

The developed procedure is feasible for screening and reviewing medications of a high number of older home care clients to identify clients with severe DRPs and provide interventions to solve them utilizing existing primary care resources.

**Trial registration:**

The study is registered in the Clinical Trials.gov (NCT02545257). Registration date September 9 2015.

## Background

The magnitude of safety risks related to medications of the older adults has been evidenced by numerous studies [1, 2], but less is known of how to manage and prevent these risks in different health care settings. Since the 1990s, both explicit and implicit criteria have been established to decrease prescribing of potentially inappropriate medicines (PIMs) for the older adults [3–5]. These criteria are useless unless they are implemented routinely throughout health care. Recently, the implementation has been facilitated through electronic databases, software applications and clinical decision support systems (CDSS), which have dramatically evolved over the last decade [6, 7]. The databases and CDSS systems can prospectively detect PIMs and other medication safety risks, but qualified healthcare professionals are needed to make the final decision using clinical judgement based on comprehensive patient information. Efficient use of these modern tools and skill-sets requires coordinated medication management processes in different healthcare settings.

Finland is one of the countries with advanced national health portals, databases and prospective screening systems for managing drug-related risks (Fig. 1) [8–11]. Within less than 20 years, a wide range of medication risk management tools have been developed, with the Finnish Medical Society Duodecim playing a major role in their development [9]. These tools are widely available in Finnish health care, including community pharmacies.

**Fig. 1 Fig1:**
[figure not shown]
Medication risk management tools and databases launched in Finland since 2004 and currently widely available in health care and community pharmacies

Even though these innovative prospective medication risk management tools and databases are widely available in Finland, they do not form an integrated medication management process. Health care providers and units work independently, without coordination, and no one seems to have clear responsibility for identifying and solving individual patients’ drug-related problems (DRPs) [12].

The aim of this study was to integrate risk assessment tools, procedures and databases available in Finland to form a coordinated medication management model (CoMM) involving home care nurses and practical nurses (PNs), physicians and community pharmacists in the medication process of older home care clients. A study design was also developed for assessing the effectiveness of CoMM.

## Methods/Design

### Context of the study and its importance for ongoing social and health services reform in Finland

Health care services in Finland are primarily funded and organized by municipalities [13]. The services are divided into primary care and specialized care services. The municipalities and individual residents may acquire services from the public and private health care providers or the third sector. Medicine supply and related pharmaceutical services for outpatients are provided by private community pharmacies. Currently, the Finnish health care system is undergoing a massive reform [14]. The goal is to improve integration between primary and specialized care and integrate social and health services from the clients’ perspective. Integration concerns service provision and funding as they both are currently fragmented.

Long-term home care services for the older adults are a critically important part of health care delivery in Finland as in many other countries [15, 16]. Currently they are mostly based on regular, even daily, encounters with home care PNs, coordinated by home care nurses. The allocation of physicians’ time for clients is limited and will become even more limited in the future as the proportion of the older adults is increasing [17]. This is putting more pressure on developing new collaborative procedures for monitoring benefits and risks of medication therapies. As part of reorganizing the care PNsʼ involvement in monitoring medication risks and benefits could be enhanced, but PNs have the very basics of relevant pharmacotherapy [18]. A need for enhancing pharmacists’ involvement in medication management of the older adults is identified [12, 19].

The aim of this study was to coordinate resources for prospective medication risk management of home care clients ≥ 65 years in primary care and to develop a study design for demonstrating effectiveness of the procedure.

### Study setting: participating organizations, health professionals and home care clients

This study is conducted within publicly funded primary care in Lohja, a municipality in Southern Finland with 47,000 inhabitants. Health care units involved in the study are: Lohja Home Care Unit, Lohja Health Center, and a private community pharmacy (Lohja 1st Pharmacy). A clinically trained researcher (TT) from the research group coordinated the development of CoMM and the design for the effectiveness study in close cooperation with the health care providers involved in home care in Lohja.

Lohja Home Care Unit is divided into five service areas, each having a leading nurse, nurses and PNs who mostly conduct home visits. Nurses consult physicians (working in the Lohja Health Center) as needed, but the physicians meet the patients infrequently. Community pharmacists from the Lohja 1st Pharmacy had primarily a standard BSc(Pharm) or MSc(Pharm) degree with long-term in-house training for geriatric pharmacotherapy and managing DRPs in the older adults, but a pharmacist with accreditation in comprehensive medication reviews (CMRs) [20] was available as needed. All these pharmacists are termed “pharmacists” in this report.

#### Participants

Home care clients were recruited in the study by nurses and PNs. They individually approached their clients and/or their closest proxy and invited them to participate in the study. Announcements in the local newspaper were also used. The recruitment process was carried out between September 2015 and December 2015. The inclusion criteria were: 1) ≥ 65 years old, home-dwelling resident; 2) receives regular home care from the city of Lohja; 3) uses at least one medicine; 4) voluntary participation, written informed consent to participate in the study given by participant or closest proxy.

### Study design

This study applied action research method to develop the CoMM. Action research method is increasingly being used in health services research [21, 22]. When applying this method, the researcher works explicitly with and for people rather than undertaking research on them [22]. The model development was theoretically guided by Reason’s systems-based risk management theory on preventing human errors [23], complemented by Hepler and Strand’s basic principles of identifying, solving and preventing DRPs [24]. Clyne’s model was applied for categorization of comprehensiveness of medication reviews [25].

#### Development process of CoMM (intervention) and study design for demonstrating its effectiveness

The goal was to construct a collaborative procedure which utilizes each profession’s resources in a rational way. The coordination of the use of the risk management tools and resources illustrated in Fig. 1 was part of the process.

The development process encompassed four main steps (Fig. 2). During each step, the coordinating pharmacist/researcher (TT) worked closely with the home care nurses and PNs, their manager (nurse), physicians involved in home care and the community pharmacists.

**Fig. 2 Fig2:**
[figure not shown]
Development process of coordinated medication management model (CoMM) using action research method (modified from Lewin 1946 [21], Meyer 2000 [22])

Exploration step (I) included orientation to each organization’s current medication management practices targeted to older home care clients. It also covered identification of medication management tools and procedures applied locally in Lohja compared to those generally available in Finland (Fig. 1). Actual tasks and responsibilities for each professional were defined in regular joint meetings with the coordinating pharmacist (TT), the pharmacy owner (ES) and the responsible nurse of home care service area (KP).

An inventory of clinical measures, used in routine clinical practice in Lohja Home Care, was conducted to include them as outcome measures in the effectiveness study design protocol. The ECHO model, which covers economic, clinical and humanistic outcomes, was applied for their selection and categorization [26]. Systematic review of Kiiski et al. (2016) [27], and other previous literature were applied to learn about experiences of rigorous study designs for assessing effectiveness of collaborative medication management models for the older home care clients.

Installation step (II) was to prepare the participating organizations for the CoMM. Home care nurses, PNs, physicians and pharmacists were informed prior to the study and encouraged continuously to comment on the model construction. Personnel training sessions needed to support the model construction were jointly planned with the researchers and home care management. The coordinating pharmacist organized trainings for PNs related to the recruitment process, medication reconciliation [28] and use of clinical tests. PNs were also trained on the content and use of the Drug-Related Problem Risk Assessment Tool (DRP-RAT) [8, 29] and about Lohja Home Care Unit’s principles in medication management [30].

Finishing the CoMM (III) aimed to decide the way to solve the identified clinically significant DRPs and allocate medication reviews according to the severity of the DRPs. In the consensus meeting home care physicians, home care managers, leading nurses, community pharmacists, coordinating pharmacist and the research group discussed to agree on tasks and to set up criteria for medication reviews and their comprehensiveness. Steps and procedures related to patient information transfer, interprofessional collaboration and adequate follow-ups were discussed.

After finishing the development of CoMM, its full operation started (IV). The coordinating pharmacist worked closely with the home care practitioners and community pharmacists, facilitating integration between stages and tasks of the health care providers involved. This enabled reflection of the model’s feasibility.

Study design for assessing effectiveness of CoMM was developed and selection of outcome measures was made in collaboration with Lohja Home Care and the research group utilizing published evidence on assessing effectiveness of medication review procedures. Selection was made considering study purposes, reliability, validity, sensitivity and specificity of measures and feasibility of carrying out the measurements in clinical practice. Measures already in use were prioritized to minimize additional work for nurses and PNs and inconvenience for the patients.

### Description of developed CoMM for home care clients (intervention)

The developed CoMM consists of five main stages in which clinically significant DRPs can be identified and solved using collaborative procedures and medication reviews (Fig. 3, Table 1). PNs were trained to observe potential medication risks on routine home visits more systematically than before and to report detected clinically significant DRPs to the coordinating pharmacist (Fig. 3: Stage I: Risk Assessment). The coordinating pharmacist prepared the cases for the triage meeting (Fig. 3: Stages I and II), in which the leading home care physician and the coordinating pharmacist decided on further actions for clients with clinically significant DRPs (50–70 cases per triage meeting of two hours). The actions included more comprehensive medication reviews according to the needs of the clients involving their own physicians and nurses/PNs. In most complicated cases also home visit and the client’s clinical interview were conducted (Fig. 3: Stage III). Based on the information gathered in Stages I-III client’s personal physician made decisions on required actions (Fig. 3: Stage IV) and follow-up was organized (Fig. 3: Stage V).

**Fig. 3 Fig3:**
[figure not shown]
Developed coordinated medication management model (CoMM) for older home care clients

**Table 1 Tab1:** Agreed tasks of each healthcare professional and tools used in the coordinated medication management model (CoMM)

Healthcare professionals	Tasks in the coordinated medication management model	Tools used
Home care nurses (practical nurses, nurses)	Medication reconciliation Medication risk assessments Clinical tests to assess clients’ functioning and disability (at baseline, 12 and 24 month follow-up)	Medication lists, usual home visits Clinical interviews with the DRP-RAT a) Measures used in usual clinical practice: functional ability (RAVA) [37], physical performance (The five-times-sit-to-stand test) [38, 39], cognitive functioning (MMSE) [40], depression (GDS-15) [41] and malnutrition (MNA) [42]. b) Added measures: difficulties related to urination (UDI-6) [43], orthostatic hypotension (3 min test) [44] and alcohol use (AUDIT-C) [45].
	Implementing medication changes and monitoring their outcomes	Regular home visits as usual Informing physicians when needed
Community pharmacists	Prescription review (PR)	Clinically significant drug-drug interactions (DDIs) (SFINX) [32] Potentially inappropriate medicines (PIMs) according to Beers 2015 criteria [46], anticholinergic and serotonergic loads of medicines (Salko) [33].
	Medication review (MR)	Patient information: medication list, DRP-RAT and glomerulus filtration rate (GFR) results Other tools used: SFINX (DDIs), Pharao (Cumulative scoring of the anticholinergicity, bleeding risk, constipation, orthostatic hypotension, prolongation of QT interval, nephrotoxicity, sedation, convulsion risk and serotonergicity of the patient’s medication) [47], Salko (PIMs) [33], Renbase (Renal function and appropriateness of doses/medicines used) [9].
	Comprehensive medication review (CMR) conducted by a qualified pharmacist (TT, SL)	Patient information: medication list, DRP-RAT and GFR results, diagnosis, laboratory test results. Tools used: As in MR, complemented by client’s clinical interview [20, 48]
Coordinating pharmacist	Trainings of the PNs for the recruitment process, CoMM and use of DRP-RAT (MD)	Meetings, discussions, personal guidance, DRP-RAT training [29]
	Coordinating and organizing processes for CoMM	Constructing the CoMM structure through observations, meetings, contacts and negotiations with organizations, health care professionals, researchers and home care clients involved, organizing processes and interactive training, providing training, guidance and feedback, reflecting the literature and guidelines on geriatric care and pharmacotherapy
	Preparing triage meetings with the leading home care physician to decide on actions for clients with clinically significant DRPs	Prescription review findings (from SFINX and Salko databases) and DRP-RAT results.
Leading home care physician	Triage meetings with the coordinating pharmacist to decide on actions for clients with clinically significant DRPs (50–70 cases per triage meeting of 2 h)	Prescription review findings (from SFINX and Salko databases) and DRP-RAT results.
Client’s personal physician	Case-conferences with pharmacists concerning clients with clinically significant DRPs identified in MR and CMR. Decisions on the medication changes and how they will be implemented.	Medication lists accomplished with the SFINX and Salko data, DRP-RAT results, results from the clinical tests, laboratory test (GFR), MR and CMR report, including client’s clinical interview.

*Abbreviations*: *DRP-RAT* Drug-Related Problem Risk Assessment Tool [31], *MMSE* Mini Mental State Examination [40], *GDS-15* Geriatric Depression Scale [41], *MNA* The Mini Nutritional Assessment [42], *UDI-6* Urinary Distress Inventory [43], *AUDIT-C* Alcohol Use Disorder Identification Test, version C [45], *SFINX* Drug-drug interaction database’s new name since March 2017 is INXBASE, *Pharao* adverse effects database’s new name since March 2017 is RISKBASE

Collaborative tasks of each healthcare professional in the developed model (Fig. 3) are described in Table 1. Nurses and PNs had a key role in clinical follow-up and identifying clients with clinically significant DRPs through gathering and bringing information about clients’ symptoms and signs by DRP-RAT. Community pharmacists’ pharmacotherapeutic skills were utilized in medication reviews at Stage III (Fig. 3). Physicians’ resources were allocated for clinical decision making at the triage stage (Stage II) and for deciding on actions for clients with complicated DRPs analyzed more in detail in prescription review (PR), medication review (MR) or comprehensive medication review (CMR). (Stage IV). The coordinating pharmacist had a key role in organizing and coordinating medication management processes between the fragmented organizations involving different health care providers, and in preparing and participating in the triage meetings followed by different level medication reviews.

### Description of study design for assessment of CoMM’s outcomes and effectiveness

Randomized controlled trial (RCT) was selected for assessing the effectiveness of CoMM.

#### Trial design

The CoMM study is a randomized controlled superiority trial with two parallel groups, a 1:1 randomization (intervention and control).

#### Randomization

Participants were randomized to an intervention group (IG) and a control group (CG) receiving standard home care. To prevent contamination between IG and CG and subsequent dilution of the intervention, participants were randomized by home care areas (2 areas to the IG, 3 areas to the CG) since each home care area has its own nursing staff. The randomization was performed by sealed envelopes. The study is considered as open-label. The IG (*n* = 104) received the intervention (CoMM) during the first year, while the CG (*n* = 87) received standard care and received the same intervention after the first year (delayed intervention as control).

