#### Data collection methods and data management

Home care nurses and practical nurses conduct clinical tests and DRP-RAT –assessments, compile medication lists and deliver the data to the research coordinator (TT). Pharmacists use case report form in medication reviews and research coordinator receives the data. Data are entered into a computerized database by the research coordinator. All patients will be given a unique study number to preserve confidentiality. The collected data will be verified for accuracy, missing data, and data consistency with the documents source (medication lists, clinical test forms).

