#### Statistical methods

Data will be analyzed on an intention to treat principle, including all randomized participants in the group to which they were randomly assigned. Also per protocol analysis to compare participants from intervention group with clinically significant medication changes conducted due to CMR, MR or PR, with control group will be performed.

The effectiveness of intervention compared to controls receiving standard home care will be first analyzed with unadjusted analysis. If there exists any group differences in participant characteristics or clinical outcomes at baseline, these variables will be included in adjusted analysis.

Descriptive statistics (mean, median or percentages as appropriate) will be used to summarize the participant characteristics and clinical outcomes. The comparison in the participant characteristics and clinical outcomes at baseline between groups will be done by two-sample t-test for normally distributed variables and by Mann-Whitney U-test for non-normally distributed variables. Chi-square test will be used for categorical variables.

Continuous outcomes will be analyzed with analysis of variance or covariance and repeated measures analysis of variance or covariance. Dichotomous outcomes will be analyzed by binary logistic regression and ordinal outcomes by cumulative logistic regression using generalized estimating equations to account for the correlation between the repeated measurements. Participants with baseline measurement and at least one follow-up measurement will be included in longitudinal analysis. Two-sided statistical tests with a 5% level of significance will be used.

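### Five home care areas were allocated 2 versus 3, but the planned 5% tests treat clients as independent and the design is labelled 1:1; how anti-conservative the tests are depends on an ICC that is not given

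*Protocol article*

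**What the plan says.** Under Study setting, the protocol article reports that "Lohja Home Care Unit is divided into five service areas". Under Randomization, "participants were randomized by home care areas (2 areas to the IG, 3 areas to the CG"), with the reason "since each home care area has its own nursing staff". The resulting groups are 104 intervention and 87 control clients, and the study is open-label.

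Trial design describes the study as a "randomized controlled superiority trial with two parallel groups, a 1:1 randomization (intervention and control") and does not mention clusters.

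Under Statistical methods, "Continuous outcomes will be analyzed with analysis of variance or covariance and repeated measures analysis of variance or covariance". Dichotomous and ordinal outcomes go to logistic and cumulative logistic regression "using generalized estimating equations to account for the correlation between the repeated measurements". Variables that differ between groups at baseline are to enter an adjusted analysis. All tests are two-sided at 5%. Home care area is not named in any model. Under Sample size, the article states that no calculation was made, so no allowance for clustering enters there either.

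**The concern.** When whole areas are allocated, the treatment contrast is a contrast between two areas and three areas. Whatever clients in one area share becomes part of the error of that contrast. The feature that led to allocation by area, a separate nursing team in each, is also a plausible source of such sharing. The teams carry out key parts of the intervention, and they also produce outcome data: "Home care nurses and practical nurses conduct clinical tests and DRP-RAT –assessments", without blinding.

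A test that counts 191 independent clients leaves the between-area variance out of its standard error. Ordinary differences between five nursing teams may then be taken for an effect of the coordinated medication management model (CoMM). This touches every between-group comparison behind the effectiveness claim.

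The 1:1 label is a separate, smaller fault. It fits neither the areas (2 to 3) nor the clients (104 to 87, or 1.20 to 1), and it obscures the cluster design. It has no numerical consequence of its own.

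**Working it through.** **Figure to reproduce.** The article states no power, effect size or ICC. The only available check is the total: 104 + 87 = 191, which agrees with the number of consented clients in the Abstract.

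**Inputs from the protocol article.** 2 intervention and 3 control areas; 104 and 87 clients (Randomization); two-sided alpha 0.05 (Statistical methods).

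**Assumptions, not in the documents.** ICC from 0 to 0.10; equal area sizes within each arm, 104/2 = 52 and 87/3 = 29; a continuous outcome with SD 1, compared unadjusted at one time point.

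**Step 1, variance as planned (independence).** 1/104 + 1/87 = 0.02111, so SE = 0.145 SD.

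**Step 2, variance with clustering.** The design effect per arm is 1 + (m − 1) × ICC, that is 1 + 51 × ICC and 1 + 28 × ICC. Variance = DE1/104 + DE2/87.

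- ICC 0.01: 1.51/104 + 1.28/87 = 0.02923, SE 0.171. Variance ratio 0.02923/0.02111 = 1.385.
- ICC 0.05: 3.55/104 + 2.40/87 = 0.06172, SE 0.248. Variance ratio 0.06172/0.02111 = 2.92.

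**Step 3, true type I error of the nominal 5% test.** 2 × [1 − Φ(1.96/√variance ratio)]. At ICC 0.01 this is 2 × [1 − Φ(1.665)] = 9.6%. The simulated column comes from the pooled t-test on area sizes 52, 52, 29, 29, 29, with 20,000 simulated trials per ICC.

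| ICC (assumed) | DE, 52 per area | DE, 29 per area | Variance ratio | SE ratio | Type I error | Simulated |
|---|---|---|---|---|---|---|
| 0 | 1.00 | 1.00 | 1.00 | 1.00 | 5.0% | 5.0% |
| 0.005 | 1.255 | 1.14 | 1.19 | 1.09 | 7.3% | not run |
| 0.01 | 1.51 | 1.28 | 1.385 | 1.18 | 9.6% | 9.7% |
| 0.02 | 2.02 | 1.56 | 1.77 | 1.33 | 14.1% | 14.2% |
| 0.05 | 3.55 | 2.40 | 2.92 | 1.71 | 25.2% | 25.7% |
| 0.10 | 6.10 | 3.80 | 4.85 | 2.20 | 37.3% | 38.1% |

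Equal area sizes are not critical. With assumed sizes of 70 and 34 against 45, 25 and 17, the error is 10.2%, 27.3% and 39.9% at ICC 0.01, 0.05 and 0.10.

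**Step 4, an analysis that respects area.** A t-test on the five area means has 5 − 2 = 3 df and critical value 3.182. Its simulated type I error was 4.4% to 4.8% for ICC 0 to 0.10. The 95% half-width is 3.182 × 0.171 = 0.54 SD at ICC 0.01 and 3.182 × 0.248 = 0.79 SD at ICC 0.05, against 1.96 × 0.145 = 0.28 SD under independence.

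**Step 5, what the randomisation alone can support.** With the 2-to-3 split taken as fixed, there are C(5,2) = 10 possible allocations. The smallest exact p-value is 1/10 = 0.10.

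**The case against.** **An analysis plan that is not shown might deal with area.** This would answer an article that was silent on methods. Here the article names the models and names the correlation that they handle. The generalised estimating equations address measurements on one client over time and leave clients in the same area independent of each other.

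**Baseline adjustment may help.** Covariance adjustment could remove part of the stable area differences, such as case mix, and so lower the residual ICC. That stands as partial mitigation. But the adjustment depends on an observed imbalance, it does not reach differences that arise after baseline, and it leaves the degrees of freedom at client level. Area is nested within arm, so a fixed area term could not be separated from treatment.

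**The size is unknown.** This stands. A reader might infer that the tests are necessarily far too optimistic, or that type I error is well above 5%. The documents do not support that as a fact: they give no ICC, and at 0.005 the error is 7.3%. Nor do they show that area differences will be read as a CoMM effect, only that they may be. The figures also do not cover the dichotomous and ordinal outcomes, or the longitudinal set, which is limited to clients with baseline and at least one follow-up.

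**Confidence intervals are not mentioned in the article.** Correct. What can be said is that any interval built on the same standard errors would be too narrow.

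**The 0.10 floor might seem to rule out a 5% superiority test.** It does not. The floor belongs to the exact randomisation test. The 3-df t-test can reach p below 0.05 and kept its level in the simulation, but it relies on a model for the area effects.

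**The true split is disclosed.** Randomization reports 2 versus 3 areas and 104 versus 87 clients, so the 1:1 label is a contradiction in wording and should not carry the weight of the point.

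**Conclusion.** The concern holds with its size left conditional. The stated analysis does not match the stated allocation: areas were randomised, clients are analysed as independent, and only correlation between repeated measurements is handled. With any positive within-area correlation the 5% tests are anti-conservative. Under the assumptions above, the true error runs from about 7% at ICC 0.005 through 10% at 0.01 to 37% at 0.10. Because areas average 29 to 52 clients, even an ICC of 0.01 nearly doubles the nominal level. The mismatch itself is certain from the text; its magnitude rests on the assumed ICC, on equal area sizes within arm and on an unadjusted continuous outcome. A between-group test at 5% remains possible, but it would rest on assumptions about area effects that five areas can hardly check. The plan should be changed before the between-group results are analysed.

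**What to change.** **Trial design.** Replace the 1:1 wording with: *cluster-randomised superiority trial of five home care areas, two allocated to intervention and three to delayed intervention.*

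**Statistical methods.** Make the primary between-group analysis respect area. The preferred form is baseline-adjusted area means compared by a t-test on 3 df. The alternative is a mixed model with a random area intercept and small-sample degrees of freedom. The area-mean version is the safer of the two, since with five areas the area variance may be estimated as zero. Do not rely on uncorrected sandwich standard errors from generalised estimating equations clustered on five areas.

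**Limitation to state.** A superiority conclusion at 5% depends on model assumptions about area effects, because an exact randomisation test has 10 allocations and cannot give p below 0.10.

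**Cost.** Recruitment and allocation are complete, so only the description and the analysis change; no new data are needed. The price is precision and a weaker claim. Relative to the independence interval, the 3-df interval is 1.9 times as wide at ICC 0.01, 2.8 times at 0.05 and 3.6 times at 0.10. It is 1.6 times as wide even at ICC 0, because only 3 df remain.
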